### Recruitment from GP referrals via the ISLAND Cognitive Clinic

All patients aged ≥ 50 years who are referred to the ISLAND Clinic by their GP with at least 3 months of cognitive symptoms, and no established diagnosis of MCI or dementia, will be invited to take part in the TapTalk study. When participants attend the ISLAND Clinic, they are routinely assessed for their capacity to consent to research as part of ethics approved ISLAND Clinic procedures [62]. A researcher will administer the TapTalk and MoCA (or RUDAS) in the same way as described for participants recruited via the RHH. The only difference is that the clinical and demographic details described on the Data Collection Form are collected routinely within the ISLAND Clinic so will be cross populated from other assessments. For all participants seen in the ISLAND Clinic who were originally recruited through the hospital, the TapTalk, MoCA (or RUDAS), demographic and clinical data will have already been collected. The main purpose of the Clinic for these participants is to provide consent to access data collected during the Clinic, clarity on the diagnosis and a management plan for their cognitive symptoms. From the aspects of the TapTalk study, this diagnosis also allows us to validate the smartphone tests against clinical diagnosis.

### Statistical analysis

We will calculate AUC for TapTalk and MoCA (or RUDAS) to predict clinical diagnosis of MCI and AD dementia (defined as AD or mixed AD/vascular); 95% confidence intervals will be obtained using bootstrapping. Covariates may include age, gender, APOE4, years of education, and handedness. We will estimate cut-off scores for TapTalk and MoCA (or RUDAS) to differentiate between cognitively unimpaired vs. MCI, and between cognitively unimpaired vs. AD using the Youden index to optimise the trade-off between sensitivity and specificity. Classification accuracy (sensitivity and specificity) using these cut-offs will be compared using McNemar’s test. Participants diagnosed with other types of dementia (such as Dementia with Lewy Bodies or Frontotemporal Dementia) will not be included in this analysis.

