#### Design

We will undertake a prospective study of 200 adults who *have cognitive symptoms* to validate TapTalk against gold-standard clinical consensus diagnosis of MCI and AD dementia. Secondary aims include determining the usability of TapTalk in a cohort with cognitive symptoms and comparing the usability and validity of TapTalk with commonly used brief screening tools. The study will be undertaken at two sites – the Royal Hobart Hospital (RHH) and the University of Tasmania ISLAND Cognitive Clinic with 100 people recruited from each site; see Fig. 5 for an overview of the study design.

The *inclusion criteria* are adults aged ≥ 50 years old with at least 3 months of persistent cognitive symptoms (patient- or family-reported).

The *exclusion criteria* are any adults who are < 50 years old, acutely unwell, have significant impairment of hand function or speech function, lack capacity to consent to the research study, or already have a known diagnosis of MCI or dementia.

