After completing the test protocol, the RA will give the participant an information leaflet on the ISLAND Clinic (https://islandclinic.utas.edu.au/) that they can pass on to their GP if they would like to have further cognitive assessments. This GP letter will include a numerical research code used during the TapTalk assessments so that, if the participant attends the clinic, their data can easily be linked. The ISLAND Clinic protocol has been described previously in Alty et al. [62]; in brief it is a state-wide cognitive clinic that provides facilities and expertise for clinical diagnosis in a ‘one-stop’ interdisciplinary model where participants will have cognitive, medical and movement assessments performed on one day. They will also have an MRI brain scan, blood tests and an array of other tests. The interdisciplinary team formulates a consensus diagnosis for each participant attending the clinic. One of the clinicians on the team delivers the diagnosis to the participant on the same day and provides a detailed management plan for the participant and GP. The Clinic is supported by research funding and is Medicare bulk-billed for participants with no out-of-pocket costs.

This means that through the standard ISLAND Clinic processes, all participants recruited through the RHH will have the opportunity to have thorough medical and cognitive assessments, including neuropsychological tests, an interdisciplinary consensus diagnosis and management plan for their cognitive symptoms [62]. The established diagnosis of ‘cognitively unimpaired’ (objectively ‘normal’ on ISLAND Clinic tests), ‘MCI’ and ‘AD dementia’ (AD and mixed AD/vascular) also allow us to validate TapTalk scores against the gold standard clinical diagnosis.

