### Sample size justification

As the conditional dependence between TapTalk and MoCA (or RUDAS) is unknown, the nominal power of the study cannot be calculated. However, Roalf et al. compared the diagnostic accuracy of MoCA with MMSE using a comparable sample size (n = 126 MCI and n = 140 healthy controls) and found a significant difference (in favour of MoCA) between the two diagnostic tests [63].

The main outcome of Study 3 will be an externally validated TapTalk smartphone test with determined precision for prospectively predicting risk of MCI and AD in adults ≥ 50 years old with cognitive symptoms. Secondly, we will have a measure of the accuracy and usability of the TapTalk smartphone test compared to MoCA in adults ≥ 50 years old with cognitive symptoms.

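### Aim 3 estimates cut-off accuracy only for unimpaired vs MCI and unimpaired vs AD, so none is planned for any impairment, or for AD dementia against everyone else, among all diagnosed participants

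*Protocol article*

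**What the plan says.** Aim 3 recruits 200 adults aged 50 or over with cognitive symptoms "to validate TapTalk against gold-standard clinical consensus diagnosis of MCI and AD dementia" (Aim 3, Design). Anyone with a known diagnosis of MCI or dementia is excluded, so diagnostic status is unknown when TapTalk is taken. The clinic then supplies three reference categories: "The established diagnosis of ‘cognitively unimpaired’ (objectively ‘normal’ on ISLAND Clinic tests), ‘MCI’ and ‘AD dementia" (Aim 3, Recruitment from the hospital).

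The Aim 3 Statistical analysis section has four relevant parts:

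- AUC: "We will calculate AUC for TapTalk and MoCA (or RUDAS) to predict clinical diagnosis of MCI and AD dementia". The comparison group is not stated, nor whether the two diagnoses are taken separately or together.
- Cut-offs for TapTalk and MoCA (or RUDAS): "to differentiate between cognitively unimpaired vs. MCI, and between cognitively unimpaired vs. AD using the Youden index".
- Use of the cut-offs: "Classification accuracy (sensitivity and specificity) using these cut-offs will be compared using McNemar’s test".
- Exclusion: "Participants diagnosed with other types of dementia (such as Dementia with Lewy Bodies or Frontotemporal Dementia) will not be included in this analysis".

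The Aim 3 Sample size justification gives the main outcome as an externally validated test with determined precision for "prospectively predicting risk of MCI and AD in adults ≥ 50 years old with cognitive symptoms". Comparison with MoCA comes second.

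**The concern.** The cut-off contrasts are written out, so this is not detail left to another document. The unimpaired-vs-AD cut-off, and the accuracy at it, are estimated with every MCI participant removed. The unimpaired-vs-MCI figures are estimated with every AD dementia participant removed. A person who presents with symptoms and no diagnosis cannot be sorted in that way before testing.

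Two accuracy questions follow from the stated main outcome: does the score separate impaired from unimpaired people, and does it separate AD dementia from everyone else diagnosed? No planned cut-off answers either. MCI is the group next to AD dementia on the continuum, and the protocol's Background cites a hand-movement measure that worsens along it. Leaving MCI out of the AD contrast therefore removes the people whom an AD cut-off is most likely to misclassify. A reader who takes the resulting specificity as AD dementia versus not AD dementia would think the test better than it is.

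**Working it through.** **Plan's own figure.** Aim 3 gives no expected AUC, diagnostic mix, effect size or power, so there is nothing to reproduce. The size of the effect has to come from assumptions, stated here.

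**Model (assumed).** One score, equal variances: unimpaired N(0,1), MCI N(dM,1), AD dementia N(dA,1). Let u, m and a be the shares of unimpaired, MCI and AD among included participants. Then:

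- Youden cut-off for unimpaired vs AD: c = dA/2
- Pairwise specificity = Φ(c); AD sensitivity = Φ(dA − c)
- Share of MCI above the AD cut-off = Φ(dM − c)
- Specificity against all non-AD = [u·Φ(c) + m·Φ(c − dM)] / (u + m)
- Pairwise AUC = Φ(dA/√2)
- AUC against all non-AD = [u·Φ(dA/√2) + m·Φ((dA − dM)/√2)] / (u + m)

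**Set 1: dA = 1.6, mix 30/45/25%, position of MCI varied.** The cut-off is c = 0.8, pairwise specificity Φ(0.8) = 0.788 and pairwise AUC Φ(1.131) = 0.871.

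Worked case, dM = 0.8:

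- Specificity = (0.30 × 0.788 + 0.45 × 0.500)/0.75 = 0.615, a drop of 0.17.
- AUC = (0.30 × 0.871 + 0.45 × 0.714)/0.75 = 0.777, a drop of 0.09.

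| MCI mean dM | MCI above AD cut-off | Specificity, AD vs all non-AD (drop) | AUC, AD vs all non-AD (drop) |
|---|---|---|---|
| 0 (same as unimpaired) | 21% | 0.79 (0) | 0.87 (0) |
| 0.4 | 34% | 0.71 (0.08) | 0.83 (0.04) |
| 0.8 | 50% | 0.62 (0.17) | 0.78 (0.09) |
| 1.2 | 66% | 0.52 (0.27) | 0.72 (0.16) |

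**Set 2: separations set through pairwise AUCs, d = √2·Φ⁻¹(AUC).** The AUC pairs (unimpaired vs MCI / unimpaired vs AD) were 0.70/0.85, 0.75/0.90, 0.80/0.95 and 0.85/0.95. The mixes (unimpaired/MCI/AD) were 33/33/33, 50/30/20, 20/50/30 and 40/40/20%.

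- Specificity at the AD cut-off is 0.77 to 0.88 in the pair and 0.52 to 0.73 against all non-AD. The drop is 0.10 (0.768 to 0.666) to 0.35 (0.878 to 0.523).
- AUC is 0.85 to 0.95 in the pair and 0.74 to 0.89 against all non-AD. The drop is 0.06 to 0.16.
- AD sensitivity is 0.77 to 0.88 in both, because leaving out MCI does not touch the AD group.

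**The MCI contrast goes the other way.** At the unimpaired-vs-MCI cut-off dM/2, sensitivity for MCI alone is Φ(dM/2) = 0.65 to 0.77 in Set 2. Counting AD dementia as well, sensitivity for any impairment is [m·Φ(dM/2) + a·Φ(dA − dM/2)]/(m + a) = 0.72 to 0.86. The pairwise figure understates it.

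**Both sets together:** a specificity drop of about 0.08 to 0.35 and an AUC drop of about 0.04 to 0.16 whenever MCI lies strictly between the other groups as assumed. There is no drop if MCI scores match unimpaired ones.

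**The case against.** The strongest reply is that nothing in the plan is mislabelled. Each contrast is named, and sensitivity and specificity are correct for that contrast. MCI and AD dementia are separate targets throughout Aim 3, and the Background treats MCI as a prodromal stage of AD. Counting MCI as a false positive is therefore not the only sensible framing, and a single pooled contrast could hide weak MCI detection behind easier AD cases. This stands, and it is why the pairwise contrasts should be kept rather than demoted.

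Four stronger readings are tempting, and the documents do not support them:

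- **A reader might infer that AD accuracy as a whole is overstated.** AD sensitivity is unchanged, and the overstatement exists only when the pairwise figure is read as AD dementia versus not AD dementia.
- **A reader might infer that the planned AUC is pairwise.** The AUC sentence leaves its contrast open, so a pooled or all-diagnosed AUC is not ruled out.
- **A reader might infer that the two cut-offs cannot be used on a patient of unknown status.** Two thresholds on one score can be applied to anyone. What is absent is a planned accuracy estimate in the mixed group. Nor does the risk that the estimated AD cut-off falls below the MCI one settle the matter. With an assumed 48/72/40 participants and empirical Youden cut-offs, this reversal occurred in 8 to 26% of simulated studies. It still occurred in 5 to 18% with the all-diagnosed contrasts, so it is mostly small-sample noise.
- **A reader might infer that the TapTalk–MoCA comparison is biased.** Both tests are compared in the same people under the same exclusion. Absolute accuracy suffers more than the head-to-head comparison.

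The reply does not supply cut-off accuracy among all diagnosed participants, and the stated main outcome needs it.

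**Conclusion.** The concern holds in limited form. Followed as written, Aim 3 gives no cut-off, sensitivity or specificity for any impairment, or for AD dementia against all other included participants, although the main outcome is prediction in symptomatic people undiagnosed at entry. The direction of the specificity and AUC gap rests on MCI scores lying between the other two groups. Its size rests on separations and mixes that the documents do not give, and on an equal-variance normal model. The ranges above therefore show that the gap can be material; they do not forecast this study. Even with the added contrasts the figures would not describe every clinic attender, because other dementias stay excluded.

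**What to change.** In the Aim 3 Statistical analysis section:

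1. Keep the two pairwise contrasts and label each as excluding the third diagnosed group.
2. Add AUC, cut-off, sensitivity and specificity, for TapTalk and for MoCA (or RUDAS), for (a) cognitively unimpaired vs MCI or AD dementia, and (b) AD dementia vs all other included diagnosed participants, MCI included.
3. State which contrast or contrasts the AUC sentence refers to.

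The participants and data are the same, and only analysis wording changes. The cost is two more contrasts to report and, if MCI scores fall in between, a less favourable AD accuracy figure.

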The RA will then administer the MoCA, a standardised brief cognitive screening test that is commonly used in clinical practice and typically takes about 10–15 min to complete [59, 60]. The addition of this established cognitive test will allow for validation of the TapTalk scores, as well as comparison of the two tests (established cognitive test vs. TapTalk) compared to the clinical diagnosis (see later, ISLAND Clinic consensus diagnosis section). The MoCA outperforms the long-established MMSE in screening for cognitive impairment [60]. However, recent data suggest cultural differences may affect performance. Should the MoCA score suggest cognitive impairment for participants from culturally and linguistically diverse backgrounds or First Nations people, additional screening will be completed using the Rowland Universal Dementia Assessment Scale (RUDAS) [61].

After the participant has completed TapTalk and the cognitive test(s), the RA will ask the participant to complete a self-report ‘User Experience Questionnaire’ (see supplementary files). If the participant prefers the RA to read the questions out to them, the RA will do so and make a note of this in the Data Collection Form. This will provide valuable information on usability of TapTalk in a clinical cohort in comparison to a standard cognitive test.

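### Aim 3 compares sensitivity and specificity by McNemar's test at Youden cut-offs tuned in the same patients, so the error rate is too high at moderate AUC and the cut-off accuracy is optimistic

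*Protocol article*

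**What the plan says.** All of this is in the protocol article, Aim 3.

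- **Cut-offs.** The Statistical analysis section says "We will estimate cut-off scores for TapTalk and MoCA (or RUDAS) to differentiate between cognitively unimpaired vs. MCI" and, for the second contrast, "between cognitively unimpaired vs. AD using the Youden index to optimise the trade-off between sensitivity and specificity". No source for the cut-offs other than the Aim 3 patients is named.
- **Comparison.** The same paragraph continues: "Classification accuracy (sensitivity and specificity) using these cut-offs will be compared using" McNemar's test.
- **Resampling.** "95% confidence intervals will be obtained using bootstrapping" stands in the sentence on the AUCs. No split sample, cross-validation or optimism correction is stated for the cut-offs or for sensitivity and specificity.
- **Size.** The Design section says "We will undertake a prospective study of 200 adults who" have cognitive symptoms, 100 from each of two sites. Patients with other dementias "will not be included in this analysis".
- **Claim.** The Sample size justification describes the main outcome of Study 3 as "an externally validated TapTalk smartphone test with determined precision for prospectively predicting risk of MCI and AD".

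Aim 1 does keep selection and testing apart: 150 of its 500 participants are held back to test cut-offs from the development model.

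**The concern.** McNemar's test asks whether two fixed classification rules differ in the same people. Here each rule is the point that maximises sensitivity plus specificity in those people. The ROC curve is flat near that maximum, so the chosen point moves a long way along the curve from one sample to the next. Two tests with the same true curve will often be cut at different points, and McNemar's test then reads the gap as a difference between the tests because its null distribution has no term for cut-off variability.

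Choosing the maximum also makes the accuracy reported at that point too high on average.

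Two results are at stake: the head-to-head statement on sensitivity and specificity against MoCA, and the published accuracy of the TapTalk cut-off, which the article would present as externally validated.

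**Working it through.** **The plan's own figure.** There is none to reproduce. The article states no error rate for this comparison and says that power cannot be calculated because the dependence between the tests is unknown.

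**Inputs from the article.** 200 recruits fall into three diagnostic groups (unimpaired, MCI, AD dementia). An even split would give 200 / 3 ≈ 67 per group before other dementias are removed and before the loss of hospital recruits who never attend the clinic for a diagnosis. Groups of 40 to 60 are therefore plausible.

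**Assumptions not in the article.** Two-sided 5% level; true AUC 0.75 to 0.95; within-person correlation 0.3 (0 and 0.6 also tried); normally distributed scores with equal variance.

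**Model.** Both tests have the same true ROC curve, so every rejection is false. The group separation is d = √2 × Φ⁻¹(AUC), and sensitivity and specificity at the best cut-off are both Φ(d/2).
- AUC 0.75: d = 1.414 × 0.674 = 0.954; Φ(0.477) = 0.683.
- AUC 0.85: d = 1.414 × 1.036 = 1.466; Φ(0.733) = 0.768.

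**Simulation (2,000 to 3,000 runs per setting).** Each test is cut at its own sample Youden point. Exact McNemar is then run on the cases (sensitivity) and on the controls (specificity).

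| Cases / controls | AUC | Sensitivity | Specificity | Either |
|---|---|---|---|---|
| 60 / 60 | 0.75 | 33% | 33% | 45% |
| 60 / 60 | 0.85 | 21% | 23% | 32% |
| 60 / 60 | 0.95 | 9% | 9% | 16% |
| 40 / 60 | 0.75 | 26% | 36% | 42% |
| 40 / 60 | 0.85 | 15% | 26% | 32% |
| 126 / 140 | 0.75 | 40% | 45% | 54% |

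Over 40 to 60 per group the rates per metric are about 26–33% at AUC 0.75, 16–22% at 0.85 and 5–11% at 0.95. Unequal groups spread the two metrics somewhat further, as the 40 / 60 rows show. The last row uses the sample size of the MoCA-versus-MMSE study that the article cites as precedent: a larger sample does not cure the problem.

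**Controls for the simulation.** With both cut-offs fixed at the same ROC point (60 or 80 per group), exact McNemar rejects in 2–4% per metric and 5–7% for either. A paired AUC test (DeLong) rejects in 4.0–5.7%.

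**Why the rates are this size.** At 60 per group and AUC 0.75, a fixed cut-off gives sensitivity a standard deviation of √(0.683 × 0.317 / 60) = 0.060. The tuned cut-off gives 0.116, a ratio of 1.93. A test that understates the standard deviation by that factor rejects when |Z| exceeds 1.96 / 1.93 ≈ 1.015, which has probability 0.31. At AUC 0.85 the figures are √(0.768 × 0.232 / 60) = 0.0545 against 0.083, ratio 1.52, probability about 0.20. This rough calculation ignores the pairing and still lands close to the simulation.

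**Optimism.** At 60 per group, AUC 0.75 and correlation 0.3, mean tuned sensitivity and specificity are 0.727 and 0.698, a sum of 1.425. The best attainable sum is 2 × 0.683 = 1.366, so the excess is 0.059. Across 40 to 100 per group at AUC 0.75–0.85 this excess is 0.04–0.07. Measured against the true accuracy of the cut-off actually chosen, which is what new patients would experience, it is larger: about 0.07–0.10 with 40 to 60 per group. A fair overall range is 0.05–0.10 on the sum, or about 0.025–0.05 per metric.

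**The case against.** Several points on the other side stand.

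- **The comparison is secondary.** The Design section lists comparison with other screening tools among the secondary aims. The first analysis named is the AUC of each test with a bootstrap interval, which uses no cut-off and is untouched.
- **The size depends on accuracy.** At AUC 0.95 with 30 per group, exact McNemar stays at 3–4% per metric. Unimpaired versus AD dementia may be little affected.
- **An unseen analysis plan may add a correction.** It may, but the article itself fixes McNemar's test at the estimated cut-offs.

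Some stronger readings are tempting, and the article does not support them.

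- *TapTalk would often be falsely declared better than MoCA.* Of the simulated studies with a false significant result, about 79–96% showed opposite directions on the two metrics. A false result of better on one and no worse on the other occurred in 1.4–3.2%. McNemar's test on pooled accuracy rejected in only 1–7%.
- *Nothing in Aim 3 is external validation.* The algorithm is chosen in Study 1 and applied to a separate symptomatic cohort, so its AUC there is external evidence, provided the score is locked and nothing in it is refitted.
- *Test and diagnosis are simultaneous, so prospective is wrong.* Up to half the sample is recruited in hospital and diagnosed later, if at all.
- *RUDAS replaces low MoCA scores and can only reverse MoCA positives.* The article calls RUDAS additional screening after the MoCA. It does not say that the score is replaced, nor that the trigger equals the Youden cut-off.
- *Cut-offs should simply be locked from Studies 1 and 2.* Those studies target p-tau positivity and CANTAB decline, not MCI or AD dementia. Fixed cut-offs also give valid comparisons only if they sit at matching ROC points. With identical curves, 60 per group and cut-offs 0.5 SD apart, McNemar's test found a difference on either metric in 66–80% of simulated studies.

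**Conclusion.** The concern holds in this limited form. The stated sequence of Youden tuning followed by McNemar's test in the same patients has the wrong error rate for the separate sensitivity and specificity comparisons. At AUC 0.75–0.85 it is several times the nominal 5%; at 0.95 the inflation is small or absent. Unimpaired versus MCI is probably the most exposed contrast, on the assumption that it is the harder one. The usual artefact is an apparent trade-off between the two tests.

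The accuracy reported at the tuned cut-off is also too high by a moderate amount and should not be called externally validated. The AUC of a score locked before Aim 3 may be.

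The exact percentages rest on the assumed AUC, correlation, group sizes, normal scores and 5% level. The direction does not: inflation persisted at correlations 0, 0.3 and 0.6, with a coarser integer-like second score (23–32% per metric at AUC 0.80, 60 per group), and with asymptotic McNemar, which rejects more often than the exact test.

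**What to change.** 1. In the Aim 3 Statistical analysis, make the paired difference in AUC (TapTalk minus MoCA) with a bootstrap 95% confidence interval the main comparison, for each contrast. Bootstrapping is already planned for the separate AUCs.
2. If sensitivity and specificity are also compared, drop McNemar's test. Resample patients with both scores kept together, re-estimate both Youden cut-offs in every bootstrap sample, and report optimism-corrected estimates and intervals for each test and for the differences. These intervals will be wide, which is the honest message about tuned cut-offs at this sample size.
3. In the Aim 3 Sample size justification, limit the claim of external validation to the AUC of the locked TapTalk score. Describe the cut-off accuracy as internally derived and optimism-corrected.

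**Cost.** A few sentences of protocol text, a little more analysis code and slightly less favourable accuracy figures. No extra patients or data are needed.

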It is conceivable that some participants will not want to know their dementia risk and this will hinder selection of participants for the clinical subset assessments. We have minimised this risk by recruiting from a study (ISLAND Project) [45] where participants understand the focus is on reducing dementia risk. It is also important to acknowledge that, as the bulk of this project relies on self-report of known neurological diagnoses, we have limited ability to make distinctions between other neurodegenerative disorders, including other forms of dementia and disorders which are correlated with dementia (e.g., Parkinson’s disease). Finally, there are risks around COVID-19 restrictions limiting recruitment or progress of the study; as most of the study is based around online movement and cognitive tests that can be completed at home, there are likely to be minimal effects and we have already collected the blood samples for p-tau 181 (and other biomarker) analyses.

In summary, this study directly addresses the critical need for population-level screening tests to detect the earliest stage of dementia. We take a completely new approach to developing a screening test to estimate the risk of AD pathology - through movement analysis, combining two simple hand- and oral-movement tests together that are sensitive across the continuum. Using movement analysis as the basis for an AD screening test has major advantages compared to cognitive tests in terms of crossing language, cultural and educational barriers; using a smartphone will overcome the barriers of other current AD biomarkers in terms of low cost, accessibility and non-invasiveness. There is thus high potential that TapTalk will provide a scalable screening approach – especially as the test equipment is already in our pockets.

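### Aim 3 leaves other dementias out of the accuracy analysis once they are diagnosed, yet states its result for all adults aged 50 or over with cognitive symptoms

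*Protocol article*

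**What the plan says.** All references are to the Aim 3 part of the protocol article unless noted.

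- **Who enters (Design).** The inclusion criteria are "adults aged ≥ 50 years old with at least 3 months of persistent cognitive symptoms (patient- or family-reported". The cause of the symptoms is not restricted. Exclusions include people who "already have a known diagnosis of MCI or dementia" and those who "have significant impairment of hand function or speech function".
- **Order of testing (the two recruitment sections).** Hospital recruits take TapTalk before any clinic visit. GP-referred recruits take it at the clinic where the consensus diagnosis is made.
- **What is analysed (Statistical analysis).** AUCs are calculated for TapTalk and MoCA (or RUDAS) "to predict clinical diagnosis of MCI and AD dementia (defined as AD or mixed AD/vascular"). Cut-offs are chosen to "differentiate between cognitively unimpaired vs. MCI, and between cognitively unimpaired vs. AD using the Youden index", and the resulting sensitivity and specificity are compared by McNemar's test.
- **Who is left out (Statistical analysis).** "Participants diagnosed with other types of dementia (such as Dementia with Lewy Bodies or Frontotemporal Dementia) will not be included in this analysis".
- **What will be claimed (Sample size justification).** The main outcome of Study 3 is a validated test with determined precision "for prospectively predicting risk of MCI and AD in adults" aged 50 or over who have cognitive symptoms. The exclusion is not repeated there.

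**The concern.** A person whose Lewy body or frontotemporal dementia is first recognised at the clinic can be eligible, enrolled and tested with TapTalk, and is then dropped because of the reference-standard result. In practice that filter is not available: whoever reads a TapTalk score in someone with undiagnosed cognitive symptoms does not know which dementia, if any, is present. The participants dropped are part of the population named in the main outcome.

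After the exclusion, the only comparison group is the cognitively unimpaired. This is a narrower spectrum than the one recruited. The Background describes the syllable-repetition tasks as sensitive motor tests used across various neurological disorders, so it is reasonable to ask how often TapTalk would be positive in a non-AD dementia. If that is more often than in unimpaired people, the reported specificity for MCI/AD will be too high for the group to which the protocol applies it. The Discussion names clinical triage and diagnosis among the uses, so the figure would be relied on in that unfiltered group.

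**Working it through.** **Plan's own figure.** There is none to reproduce. The protocol gives no expected accuracy, case mix or number of exclusions for Aim 3, and says that power cannot be calculated.

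**Populations side by side.**

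| | Other dementias included? |
|---|---|
| Enrolment (Design, recruitment sections) | Yes, if not already diagnosed and no other exclusion applies |
| AUC, cut-offs, McNemar comparison (Statistical analysis) | No |
| Main outcome statement (Sample size justification) | Not excluded |

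The second and third rows do not match. This needs no assumption.

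**Direction and possible size (hypothetical).** Take AD dementia as the target and set MCI aside. The non-target group is then the unimpaired plus the other dementias. All inputs are assumptions:

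- unimpaired participants, n_u = 60
- specificity among them, 0.80 (20% false positives)
- other dementias, n_o = 20
- TapTalk positivity among other dementias, p, varied

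Specificity with other dementias kept = [n_u × 0.80 + n_o × (1 − p)] / (n_u + n_o)

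- p = 0.20: (48 + 16)/80 = 0.80, no change
- p = 0.50: (48 + 10)/80 = 0.725, about 0.73
- p = 0.90: (48 + 2)/80 = 0.625, about 0.63

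The same formula can be written as 0.80 − w × (p − 0.20), with w = n_o/(n_u + n_o) = 20/80 = 0.25. The sign depends only on whether p exceeds the false-positive rate in the unimpaired. At p = 0.10 the result would be 0.80 + 0.025 = 0.825, so the planned analysis would understate specificity.

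**Varying the number of other dementias (n_u = 60).**

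| n_o | p = 0.20 | p = 0.50 | p = 0.90 |
|---|---|---|---|
| 10 | 0.80 | 53/70 = 0.76 | 49/70 = 0.70 |
| 20 | 0.80 | 58/80 = 0.73 | 50/80 = 0.63 |
| 30 | 0.80 | 63/90 = 0.70 | 51/90 = 0.57 |

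**Varying the number unimpaired.** Let the unimpaired be 25% to 40% of the 200 participants (50 to 80 people), with 20 other dementias:

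- p = 0.50: (40 + 10)/70 = 0.71 to (64 + 10)/100 = 0.74
- p = 0.80: (40 + 4)/70 = 0.63 to (64 + 4)/100 = 0.68

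Sensitivity for AD does not change in any of these, because other dementias are not in the target group.

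**The case against.** **The rule is open and the contrasts are legitimate.** The exclusion is stated plainly, and unimpaired versus MCI and unimpaired versus AD are reasonable questions. Both points stand, and the contrasts should stay. Supplementary tables may also sit in a fuller document that is not shown, so the lack of an all-comers table in an article is not by itself a fault. What remains is that this article fixes both the exclusion and the main outcome statement, and the two name different populations.

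**The direction is presumed.** A reader might infer that the plan is bound to overstate accuracy. The documents do not support that. They give no TapTalk positivity in Lewy body, frontotemporal or any other non-AD dementia. TapTalk is also not a raw score of motor abnormality: its algorithm is to be developed against blood biomarkers of AD. If positivity in other dementias equals the false-positive rate in the unimpaired, specificity does not move. This objection stands, so the overstatement is conditional.

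**Entry criteria may already remove some of these cases.** People with significant hand or speech impairment are excluded before testing. This may reduce the effect by an unknown amount. It would not remove other dementias with milder motor signs or none.

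**The Discussion might seem to concede the point.** It says that "we have limited ability to make distinctions between other neurodegenerative disorders", and a reader might take this as an admission that TapTalk cannot separate AD from other dementias. The sentence gives a different reason, reliance on self-reported neurological diagnoses in most of the project. Aim 3 has a consensus diagnosis, so the sentence does not bear on this exclusion either way.

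**Predictive value.** A reader might also want to say that the positive predictive value is inflated. The plan lists AUC, cut-offs, sensitivity and specificity, not predictive value, so that is no criticism of a planned result.

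**Other dementias need not be errors.** For triage of any cognitive impairment, a positive TapTalk in another dementia is a correct flag. It is a false positive only against the stated MCI/AD target. This is why the fix includes both definitions. MoCA may be abnormal in these people too, so the TapTalk–MoCA comparison may be affected less than TapTalk's absolute accuracy.

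**Conclusion.** The concern holds as a mismatch between analysis and claim. The exclusion is conditional on the reference standard and cannot be applied when the test is used, and the main outcome statement covers a population that includes the people excluded. That much follows from the text alone.

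Whether specificity is overstated, and by how much, is unknown. It is overstated only if other dementias test positive more often than unimpaired participants, which is plausible for a motor test but not shown. With 60 unimpaired at specificity 0.80 and 20 other dementias, and MCI set aside, the figure would lie between 0.80 (20% positive) and 0.63 (90% positive). Every input to that range is assumed, so it shows only that the effect could matter, not that it will.

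**What to change.** 1. Keep the two planned contrasts, unimpaired versus MCI and unimpaired versus AD.
2. Pre-specify an additional analysis of all participants who receive a consensus diagnosis. Count other dementias as target-negative for MCI/AD, and show their number and TapTalk positivity in a separate row.
3. Add any cognitive impairment versus unimpaired, where other dementias count as impaired.
4. Base the main outcome statement for adults with cognitive symptoms on the analysis in step 2. If that analysis is not wanted, restrict the statement to unimpaired versus MCI/AD with other dementias excluded.

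No new participants or tests are needed, since TapTalk results and diagnoses for these people will arise under the existing design. The cost is a little more analysis and possibly a less favourable specificity. With few other dementias, their positivity will be imprecise and should carry a confidence interval.
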